### Sample size calculation

Two hundred and twenty-two participants are needed (111 for intervention, 111 for control at a 1:1 case to control ratio) to attain 80% power, 95% level of significance and 20% dropout rate in a population with an expected population standard deviation of 1.5, and an allowable difference of 0.01 to detect a change of 0.5% change in HbA1c concentration. We plan to train 70 lay health workers on a 1:4 lay health worker to patient ratio, and assuming a 20% dropout rate.

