In order to compare the effectiveness of intervention between control and the intervention group at the exit assessment of intervention (6^th^ month), we will use repeated-measures Analysis of Variance (ANOVA) for parametric outcomes. We will consider the measures of data at baseline (0^th^ month) and covariates that are imbalanced in control and intervention groups when conducting ANOVA, and the effect size will be estimated by calculating the Cohen's *d* value. For non-parametric variables, the Friedman test will be done, and Kendall's W value will be produced for effect size estimation. For ordinal data, we will use Generalized Estimating Equations to compare groups at each follow-up (0^th^ month, 6^th^ month, and 12^th^ month), allocation group (intervention and wait-list control), time by group interaction, covariates that are imbalance between groups, and important socio-economic variables including sex, age, and education level. We will use an identify link function given a normal distribution of the captioned outcome. Also, Kaplan-Meier curves will be drawn to capture the comparison of diabetes-free survival in the intervention and control group. The level of significance is set at 5% m and *post-hoc* adjustment will be applied for multiple comparisons. Multiple imputations will be used whenever appropriate for missing data. In this analysis, all statistical analyses will be conducted using R and RStudio, and the Cohen's *d* value will be estimated using G^*^Power.

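### The 222 participants do not give the stated 80% power after 20% dropout: two-sided power on the stated SD and difference is about 60%

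*Protocol article*

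**What the plan says.** The Sample size calculation section of the protocol article gives the total and its inputs together. The size is "111 for intervention, 111 for control at a 1:1 case to control ratio", chosen "to attain 80% power, 95% level of significance and 20% dropout rate in a population with an expected population standard deviation of 1.5", with "an allowable difference of 0.01 to detect a change of 0.5% change in HbA1c concentration".

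The Data analysis section adds two relevant facts. On the error rate: "The level of significance is set at 5" per cent. On the test, for the comparison at month 6: "we will use repeated-measures Analysis of Variance (ANOVA) for parametric outcomes", with the baseline measurement taken into account. Neither section says whether the test is one- or two-sided, and neither gives a correlation between baseline and month 6. Table 1 lists 222 as the target sample size and HbA1c as the primary outcome.

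**The concern.** The paragraph supplies every input of the usual two-mean formula except sidedness, so its result can be checked directly. A standardised difference of 0.5/1.5 = 0.33 is modest, and 111 per arm looks small for it even before anyone drops out. The figure is close to what a one-sided test needs with no losses, which suggests that the 20% allowance named in the same sentence was never applied.

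At stake is how a null result would be read. If readers accept 80% power, they will take a non-significant HbA1c result as fair evidence against a 0.5-point benefit. At 60% power a true effect of that size is missed about 40% of the time, twice the rate implied. The Data collection, management and monitoring section also allows stopping for futility, and an overstated design power could mislead that judgement.

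**Working it through.** **Inputs**

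- From Sample size calculation: SD σ = 1.5; difference δ = 0.5; power 80%; dropout 20%; 111 per arm, 1:1.
- From Data analysis: α = 5%. (The sample size paragraph calls this a 95% level of significance, evidently meaning 95% confidence.)
- Assumption: two-sided, because an ANOVA F test is non-directional and no one-sided test is mentioned. One-sided results are shown as well.

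**Step 1. Try to reproduce 111 per arm**

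n per arm = 2(z_α + z_β)²σ²/δ², where σ²/δ² = 2.25/0.25 = 9.

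| Version | Calculation | Evaluable per arm | Enrolled total after n/(1 − 0.2) |
|---|---|---|---|
| Two-sided 5% | 2 × (1.960 + 0.8416)² × 9 = 141.3 | 142 | 2 × 178 = 356 |
| One-sided 5% | 2 × (1.645 + 0.8416)² × 9 = 111.3 | 112 | 2 × 140 = 280 |

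The t-test versions are 142.2 and 112.0 per arm. The stated 111 is met, to rounding, by the one-sided row before any dropout allowance. Neither row gives 222 once dropout is included. The looser inflation n × 1.2 still gives 342 two-sided and 270 one-sided.

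**Step 2. Power that 222 delivers**

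After 20% dropout, 111 × 0.8 = 88.8, about 89 per arm.

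- Standard error = 1.5 × √(2/89) = 0.225, and 0.5/0.225 = 2.22.
- Two-sided power = Φ(2.22 − 1.96) = 60.4% (t-test 59.9%).
- One-sided power = Φ(2.22 − 1.645) = 71.9% (t-test 71.6%).
- With no dropout at all (111 per arm): 70.0% two-sided (t-test 69.6%), 79.9% one-sided.

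**Step 3. Detectable difference**

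At 89 per arm, two-sided, 80% power: (1.960 + 0.8416) × 0.225 = 0.63 points.

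**Step 4. Does the 0.01 allowable difference explain it?**

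Its role is not defined. Taking it off δ (0.49) raises the requirement to 148 evaluable per arm and gives 58.7% power at 89 per arm. Adding it (0.51) lowers the requirement to 136 and gives 62.1%. Either way power moves by less than 2 percentage points.

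**Step 5. What would make 80% true at 89 per arm, two-sided?**

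- An SD of about 1.18 to 1.19 instead of 1.5; or
- baseline-adjusted ANCOVA (variance factor 1 − ρ²) with ρ ≥ √(1 − 88.8/141.3) ≈ 0.61; or
- a change-score comparison (variance factor 2(1 − ρ)) with ρ ≥ 1 − 88.8/(2 × 141.3) ≈ 0.69.

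Power at 89 per arm (t-test) if 1.5 is the cross-sectional SD:

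| ρ | ANCOVA | Change score |
|---|---|---|
| 0.5 | 72% | 60% |
| 0.6 | 79% | 70% |
| 0.7 | 87% | 81% |

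**The case against.** Four points can be made for the plan.

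1. **Sidedness is not stated**, and the trial's hypothesis is directional, so 60% depends on an assumption. This is true, and the one-sided figure of about 72% should be given beside it. It does not save the statement: 72% is still below 80%, and a one-sided design with the stated dropout needs 280.

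2. **The planned analysis already takes account of baseline**, so an unadjusted month-6 comparison may understate its power. This is the strongest point. With a high enough correlation the trial could reach 80%, so the 40% miss rate applies to the stated SD without adjustment. But the gain depends on an unstated correlation. A repeated-measures ANOVA read through its time-by-group term is a change-score comparison, which at a correlation of 0.5 gains nothing over the unadjusted test. If 1.5 is already the SD of change, the 60% stands as it is.

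3. **The origin of 111 is inference.** Strictly, 111.3 rounds up to 112, and other faulty routes could also land on 111. This stands, so one can say only that the dropout allowance appears not to have been applied. The shortfall does not depend on how the figure arose.

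4. **The article condenses a fuller protocol**, where the 0.01 may be explained. That is a reason to allow defining it as an alternative to deleting it. It does not excuse a total that conflicts with the inputs printed beside it.

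**Conclusion.** The concern holds. With SD 1.5, a 0.5-point difference, a two-sided 5% level and 20% dropout, 222 participants give about 60% power, not 80%. The number needed would be 356. The difference detectable with 80% power is 0.63 points.

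The 60% assumes a two-sided test and no variance reduction from baseline. On a one-sided reading it is about 72%. With baseline adjustment, power reaches 80% only at a correlation of about 0.61 (ANCOVA) or 0.69 (change score), which the article does not claim. No multiplicity allowance is included. The text names two primary outcomes, and at α = 0.025 power would fall further, to about 49%. The statement is wrong as written and must be corrected.

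**What to change.** Keep 222 and correct the sample size paragraph. Suggested wording:

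> A total of 222 participants will be randomised (111 per arm). Allowing for 20% dropout, about 178 will be evaluable. This gives about 60% power at a two-sided 5% level for a between-group difference of 0.5 HbA1c percentage points with SD 1.5, and 80% power for a difference of 0.63.

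In addition:

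- If the power claim is to rest on baseline adjustment, specify the analysis as ANCOVA, state and justify the assumed correlation, and quote the resulting power (about 72%, 79% or 87% at correlations of 0.5, 0.6 or 0.7).
- State that the test is two-sided and write the significance level as 5%.
- Delete the 0.01 allowable difference, or define it if the full protocol gives it a role.

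The cost is one rewritten paragraph, and matching text in the registry if a power statement appears there; the target of 222 in Table 1 is unchanged. The declared power becomes less favourable, and no extra participants are needed. Enrolling about 356 would also resolve the conflict, but at the cost of 134 more participants (356 − 222).

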### Data collection, management and monitoring

There will be at least two time points for data collection of this intervention trial as demonstrated in Figure 1. For each assessment, the personal information of the participants will be collected through an electronic survey form that is directed link to an encrypted, private domain hosted by the Chinese University of Hong Kong. All information that contains the identification of the participants will be stored separately, and link with the main dataset with a unique identifier. The file containing the personal information of the participants and their corresponding identifier will only be accessible to the research team members. All data will be destroyed 5 years upon the completion of results dissemination of this study.

Data monitoring will be done by an epidemiologist that is independent of the sponsor for this trial. An interim analysis will be done upon the competition for the first block of intervention to evaluate the effectiveness, and to manage and report any adverse events or unintended of the interventions. Stopping rule will be employed to terminate this trial stop if there is evidence of futility or severe and serious adverse reactions due to intervention. For participants who discontinue from intervention, their reasons of discontinuation will be collected. Results of effectiveness, adverse events, and unintended outcomes of this intervention will be reported and disseminated through publishing in open-access, peer-reviewed journals.

### Data analysis

We will adopt both qualitative and qualitative approaches to evaluate the impact of lay health worker intervention in pre-diabetes management in this trial.

A quantitative methodology will be adopted to evaluate the intervention effectiveness by performing group-wise comparison of the primary and secondary outcomes in this study. A CONSORT flowchart will be adopted to present the progress and of this trial. We will adopt an intention-to-treat approach in conducting the analysis, with sensitivity analysis to be done with non-ignorable missing data. Descriptive statistics will be produced for primary and secondary outcomes depending on their measurement scale and data distribution to allow meaningful interpretation. Histogram of the data distribution will be plotted to examine whether the data is parametric, or non-parametric. We will produce mean and standard deviation for parametric data, and use median and inter-quarter range for non-parametric data. Number and percentage will be quoted for ordinal and nominal data. Standardized mean differences of each variable will be produced to evaluate the balance in control and intervention groups, with a value larger than 0.1 indicating an imbalance between groups.

In order to compare the effectiveness of intervention between control and the intervention group at the exit assessment of intervention (6^th^ month), we will use repeated-measures Analysis of Variance (ANOVA) for parametric outcomes. We will consider the measures of data at baseline (0^th^ month) and covariates that are imbalanced in control and intervention groups when conducting ANOVA, and the effect size will be estimated by calculating the Cohen's *d* value. For non-parametric variables, the Friedman test will be done, and Kendall's W value will be produced for effect size estimation. For ordinal data, we will use Generalized Estimating Equations to compare groups at each follow-up (0^th^ month, 6^th^ month, and 12^th^ month), allocation group (intervention and wait-list control), time by group interaction, covariates that are imbalance between groups, and important socio-economic variables including sex, age, and education level. We will use an identify link function given a normal distribution of the captioned outcome. Also, Kaplan-Meier curves will be drawn to capture the comparison of diabetes-free survival in the intervention and control group. The level of significance is set at 5% m and *post-hoc* adjustment will be applied for multiple comparisons. Multiple imputations will be used whenever appropriate for missing data. In this analysis, all statistical analyses will be conducted using R and RStudio, and the Cohen's *d* value will be estimated using G^*^Power.

We will use a mixed-method approach to conduct the process evaluation on the participants. Quantifiable, routine data will be collected to evaluate the output of this intervention in corresponding to the five components of this intervention as described in Table 2, following with a *t*-test to compare intra-groups estimates to allow meaningful interpretations at the 6^th^ and 10^th^ month. The results from quantitative study part will provide a description for the overall execution of the intervention, which inform the answer for the following research questions: (1) what outputs were delivered to achieve the five components of the interventions; and (2) to which extend did the different stakeholders (study participants, healthcare worker, and lay health workers) complete/ adhere to the intervention? In complimentary to the quantitate research, the qualitative part of the mix-method study will be conducted in parallel. Two rounds of qualitative semi-structured, auto-taped individual interviews will be conducted at 6^th^ months (the completion of wait list control period) and 12^th^ month (project endpoint), to collect feedbacks from different stakeholders involved in this project. Project staffs (*n* = 2), lay health workers (*n* = 10), healthcare professionals participated (*n* = 5), NPO collaborators (*n* = 5) and study participants (*n* = 10) will be invited to participate in this study. Each individual interview will last for 1–1.5 h, with the following research questions to be answered: (1) what are the feedback and major concerns of the participants of the programme; (2) how to address these concerns in the second cycle of intervention?; (3) what are the facilitators and barriers in the programme delivery; and (4) how to enhance the facilitators or mitigate the barriers?, as guided by the *Consolidated Framework for Implementation Research* (37). Detailed interview questions can be found in Supplementary material S5. All the interviews will be conducted by research staff that is not involved in the delivery of this trial to ensure impartiality.

**Table 2 T2:** Outline of the process evaluation: output indicators.

**Component**	**Output**	**Indicators**	**Source of data**
1. Lay health worker training	More trained workers	Number of training sessions conducted	Administrative data
		Number of total lay health workers trained	Administrative data
	Lay health workers being more confident to lead intervention	Knowledge, attitude and behavior in leading an intervention	Self-administered survey before and after training
2. Health professional training	More health professionals are equipped with the necessary knowledge to co-work with lay health workers	Number of training sessions conducted	Administrative data
		Number of health professionals trained	Administrative data
		Knowledge, attitude and confidence in collaborating with lay health workers	Self-administered survey before and after training
3. Formulation of targeted care plans	Tailored care plan built for participants	Number of health need assessments conducted	Administrative data
		Number of targeted care plans formed	Clinical and service record
		Completion rate of designed health goals	Clinical and service record
4. Case management	Close and tailored case management for participants	Number of families followed-up by lay health workers	Administrative data
		Number of lay health workers follow-up conducted	Administrative data
		Number of biweekly reviews meeting conducted between lay health workers and nurse/ dietitian	Administrative data
		Number of families followed-up by the same lay health workers	Administrative data
5. Financial subsidy for lay health workers	More lay health workers recruited	Number of lay health workers recruited	Administrative data
	Sustainable service model	Proportion of lay health workers that finished the 6-months follow-up	Administrative data

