### Randomization and binding

This study will adopt wait list control with open labels, as binding is not possible. The sequence of subjects receiving interventions will be determined by randomization after the informed consent is being collected, of each slots of intervention will be separated by 6 months of waiting period. Statisticians independent from the project team will be given randomly generated treatment allocation within sealed, opaque envelops. During the initial health assessment, one of the envelops will be drawn and the participant will be allocated with the drawn sequence after they consent to participate in this trial. During the waiting period, the experimental group of subjects will be allocated to usual care with no intended treatment given.

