### Primary and secondary outcomes

This controlled trial will use a wide range of clinical and patient-reported outcomes measures to assess the cost-effectiveness of this intervention. The outcomes are set with reference to the *Medical Research Council framework for evaluating complex intervention* (31) and on the *American Diabetes Association's Standards of Medical Care in Diabetes 2021* for diabetes research (32).

We have two primary outcomes in this trial. Glycated hemoglobin (HbA1c) will be measured by self-test kit (Polymer Technology Systems Inc., Whitestown USA), and fasting blood sample for plasma glucose will be measured by blood glucose monitor (ForaCare Inc, Moorpark USA).

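### For continuous outcomes, including both primaries, a histogram decides the test and the effect measure, so the primary analysis and its estimand are not fixed in advance

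*Protocol article*

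**What the plan says.** All places are in the protocol article.

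- **Scope.** Data analysis describes effectiveness as "performing group-wise comparison of the primary and secondary outcomes in this study". Primary and secondary outcomes states "We have two primary outcomes in this trial": HbA1c and fasting plasma glucose, both continuous.
- **Labelling rule.** "Histogram of the data distribution will be plotted to examine whether the data is parametric, or non-parametric". The sentence stands among the descriptive statistics, and the next one uses the label to choose mean and SD or median and inter-quartile range.
- **Test rule.** Later in Data analysis the same label selects the effectiveness test: "we will use repeated-measures Analysis of Variance (ANOVA) for parametric outcomes", with Cohen's d as effect size; and "For non-parametric variables, the Friedman test will be done", with Kendall's W as effect size.
- **Outside the rule.** "For ordinal data, we will use Generalized Estimating Equations", so ordinal outcomes are assigned by measurement scale. Diabetes-free survival is shown by Kaplan-Meier curves.
- **Blinding.** Randomization and binding: "This study will adopt wait list control with open labels, as binding is not possible".
- **Sizing.** Sample size calculation uses a 0.5-point change in HbA1c and an SD of 1.5, with 111 per arm and 20% dropout.

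No test is named for HbA1c or for fasting glucose as such.

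**The concern.** A confirmatory analysis should be known before the outcome data are. Here the two labels do not lead to two versions of one analysis. They lead to different hypotheses on different scales. If HbA1c is labelled non-parametric, the headline result becomes a Friedman test with Kendall's W. It can no longer be set against the 0.5-point difference that justified the sample size, and it does not answer whether the lay health worker arm did better than the wait-list arm.

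The article does more than leave the test open for a later document. It states a rule, and following that rule can produce this outcome. Because treatment is open label and no masked distribution check is described, the rule also leaves room for a choice made with the results in view.

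**Working it through.** **1. The scale on which the trial was sized.** Inputs from Sample size calculation: difference 0.5, SD 1.5, 80% power, 5% level. The two-mean formula per arm is n = 2(z_alpha + z_beta)² × SD² / difference², and SD²/difference² = 2.25/0.25 = 9.
- Two-sided: 2 × (1.960 + 0.842)² × 9 = 141.3, so 142 per arm.
- One-sided: 2 × (1.645 + 0.842)² × 9 = 111.3, so 112 per arm.

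The stated 111 per arm lies next to the one-sided value before any dropout allowance. With 20% dropout the formula gives 178 per arm two-sided or 140 one-sided, so the stated total of 222 is not reproduced. That mismatch is a separate matter on which this point does not depend. What matters here is that the inputs (a difference in HbA1c units and an SD) define a mean-scale target. After 20% dropout, 111 × 0.8 = 88.8, or about 89 per arm.

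**2. What each branch tests at months 0 and 6.**
- *ANOVA branch.* With two time points, the group-by-time test is the comparison of mean change between arms. It addresses the target.
- *Friedman branch.* Values are ranked within each participant. With m participants, of whom P increase, the statistic is Q = (2P − m)²/m on 1 degree of freedom, and Kendall's W = Q/m. Allocation appears in neither. If the same proportion q increases in both arms, Q = m(2q − 1)², which can be large although the arms do not differ.

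**3. Type I error of the switch.** These are simulations with no difference between arms. Skew and correlation are assumptions, because the article gives neither. Set-up A: 89 per arm, SD 1.5, correlation 0.6, normal or lognormal (log-SD 0.8), 6,000 runs. Set-up B: 5 + lognormal (sigma 0.6), correlation 0.7 on the log scale, 89 and 111 per arm, 4,000 to 6,000 runs. The valid rank test used is Mann-Whitney on change. The mean test is ANOVA group-by-time in A and ANCOVA in B.

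| Procedure | Set-up A | Set-up B |
|---|---|---|
| One pre-named mean test | 4.5–5.3% | 5.1–5.4% |
| Choice by shape only | 4.6–5.3% (skewness cut) | 4.7–5.0% (normality test) |
| Smaller of the two p-values | 5.8–6.3% normal; 6.9–7.5% skewed | 7.6–8.2% |

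With milder skew, where the label itself is uncertain (29–80% of trials labelled non-normal), the shape-only choice gave 4.8–5.6%. Simulation error is about 0.3 percentage points near 5%: √(0.05 × 0.95/6000) = 0.0028. Neither the ANCOVA test nor the rank test on change depends on the measurement unit, so set-up B carries over to fasting glucose if its shape and correlation are similar.

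**4. Friedman as named.** In set-up A, let both arms fall equally by 0.1 to 0.2 (assumed). Friedman over all participants then rejects in 11–33% of trials (normal) or 34–87% (skewed). These are rejections of no change over time. They become false positives only if reported as an effect of the intervention.

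**5. Is a switch needed?** In set-up B normality was rejected in 100% of trials, yet the baseline-adjusted mean comparison held 5.1–5.4%. Strong skew at these sizes is no reason to leave the mean scale.

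**The case against.** The strongest objection is that a reader might infer that the histogram rule itself raises the false-positive rate. The article does not support that. It describes a choice by distribution, not by result, and a shape-only choice between valid tests costs nothing measurable. The 6% to 8% belongs to reporting whichever test gives the smaller p-value, which the article nowhere proposes. This stands, and the point does not rest on inflation.

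A reader might also infer that every outcome is affected. That is wrong, because ordinal outcomes go to GEE by scale. Nor does the article say that the histogram is viewed by arm or with allocation known: open-label treatment allows this but does not show it. A numeric cut-off and the timing of the check may properly sit in an analysis plan, so their absence is not counted here.

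It can further be said that with clearly skewed data the label is never in doubt, so two analysts would agree. That is fair for strong skew, but they would then agree on the Friedman branch, which does not compare the arms. Finally, Mann-Whitney is not in the plan. It stands in the simulations as a valid rank test in order to isolate the cost of switching.

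The change of hypothesis and scale between the branches survives all of this.

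**Conclusion.** The point holds for continuous outcomes, including both primaries. As written, a histogram decides whether the HbA1c and fasting glucose results are mean comparisons between arms or Friedman tests with Kendall's W. In the second case the analysis leaves the 0.5-point mean difference used for sizing and, with the test as named, leaves the comparison of arms.

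The damage is to the estimand and to pre-specification. It is not an automatic loss of the 5% level: a purely shape-based choice between valid between-arm tests stays at about 4% to 5.6%, and a result-driven one reaches roughly 6% to 8%. Those figures rest on assumed skew, on assumed correlations of 0.6 to 0.7, and on 89 to 111 per arm. The conclusions about estimand and hypothesis need none of these assumptions. The change should be made. It is cheap and does not alter the sample size.

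**What to change.** In Data analysis, stop using the histogram to choose tests.

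- **Primary analysis.** For HbA1c and for fasting glucose, state the between-arm difference in means at month 6, adjusted for the baseline value (ANCOVA with robust standard errors), whatever the distribution looks like. Report it in the outcome's own units with a confidence interval.
- **Histograms.** Keep them for describing the data and for checking model residuals.
- **Sensitivity.** Name one between-arm rank analysis, for example Mann-Whitney on change from baseline, and state that it cannot replace the primary result. It takes the place of Friedman and Kendall's W for the comparison of arms.

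The cost is rewording one paragraph. It needs no new data, visits or participants, and slightly less analysis work.

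### Covariates for the ANOVA are chosen by a baseline standardised difference above 0.1, which chance alone exceeds for about half of variables, and the role of baseline in that model is left unclear

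*Protocol article*

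**What the plan says.** All the relevant text is in the Data analysis section of the protocol article.

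- Balance screen: a standardised mean difference is produced for every variable to judge balance between the arms, "with a value larger than 0.1 indicating an imbalance between groups". The variables to be screened are not listed.
- Model at month 6: "we will use repeated-measures Analysis of Variance (ANOVA) for parametric outcomes". HbA1c is continuous, so it falls here unless its histogram is judged non-parametric.
- Use of the screen, and of baseline: "We will consider the measures of data at baseline (0^th^ month) and covariates that are imbalanced in control and intervention groups when conducting ANOVA".
- The only covariates named in advance appear in the sentence on Generalized Estimating Equations for ordinal data: "important socio-economic variables including sex, age, and education level". That model also takes the imbalanced covariates.

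The Sample size calculation section gives the arm sizes ("111 for intervention, 111 for control at a 1:1 case to control ratio") and the design assumptions ("to attain 80% power, 95% level of significance and 20% dropout rate"), with a standard deviation of 1.5 and a difference of 0.5% in HbA1c.

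**The concern.** After proper randomisation every baseline difference is due to chance. A rule that admits a covariate because its difference passes a cut-off therefore selects on chance. It does not ask whether the covariate predicts the outcome, which is the reason to adjust. A strong predictor of HbA1c with a difference of 0.09 stays out, and an irrelevant variable with 0.11 goes in. If the cut-off is low relative to sampling error, this happens to a large share of variables. The model for a primary outcome is then unknown until the baseline data have been seen, in an open-label trial.

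The second matter is baseline itself. In a repeated-measures ANOVA, baseline is normally one of the measured occasions, yet the article also says that baseline will be considered in the ANOVA alongside the covariates. The two readings are different analyses. With one baseline and one follow-up value, one of them is less precise than the other.

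**Working it through.** **Inputs from the article:** threshold 0.1; 111 per arm; 20% dropout; SD 1.5; difference 0.5; significance level 5%.

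**Assumptions:** the threshold applies to the absolute difference; the test is two-sided; 111 × 0.8 = 88.8, taken as 89 per arm after dropout; the correlation rho between baseline and month-6 HbA1c is 0.4 to 0.8. The article gives no rho and derives no figure of its own for the balance rule, so there is none to reproduce. The sample size is used only as an input.

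**1. How often chance passes the threshold.** Under randomisation a standardised difference is approximately normal with mean 0 and standard error sqrt(2/n), n per arm.

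- n = 111: SE = sqrt(2/111) = 0.134; 0.1/0.134 = 0.745; P(|Z| > 0.745) = 45.6%.
- n = 89: SE = sqrt(2/89) = 0.150; 0.1/0.150 = 0.667; P(|Z| > 0.667) = 50.5%.

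Simulation gave 45.6% and 50.2% for normal variables, and 44.4% and 48.6% for binary variables with 30% prevalence. If 10 independent variables were screened (an assumed number), 4.6 to 5.0 would be flagged on average. At least one would be flagged with probability 1 − (1 − 0.456)^10, which is over 99%.

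**2. What the role of baseline changes.** Take one baseline and one follow-up value with common variance σ².

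- Baseline as a repeated measure: the group-by-time test is the test on change scores, with variance per participant 2σ²(1 − rho).
- Baseline as a covariate for the month-6 value (ANCOVA): variance σ²(1 − rho²).
- Ratio of change-score to ANCOVA variance: 2(1 − rho)/(1 − rho²) = 2/(1 + rho). Equivalently, ANCOVA has (1 + rho)/2 of the change-score variance.

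Power is for 89 per arm, SD 1.5, difference 0.5, two-sided 5%, from the t distribution. The normal approximation differs by less than one percentage point.

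| rho (assumed) | ANCOVA variance as share of change-score variance | Power, change score | Power, ANCOVA |
|---|---|---|---|
| 0.4 | 0.70 | 52% | 67% |
| 0.5 | 0.75 | 60% | 72% |
| 0.6 | 0.80 | 70% | 79% |
| 0.7 | 0.85 | 81% | 87% |
| 0.8 | 0.90 | 94% | 96% |

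For example, at rho = 0.5 the change-score SD is 1.5 × sqrt(1.0) = 1.5, with SE 1.5 × sqrt(2/89) = 0.225. The ANCOVA SD is 1.5 × sqrt(0.75) = 1.299, with SE 0.195.

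**The case against.** **On the covariate rule.** Adjusting for baseline covariates, even those flagged by chance, still targets the treatment effect. No bias or inflation of type I error has been shown or calculated here. A numeric cut-off stated in advance is also mechanical, which limits discretion. The list of variables to screen is commonly left to the analysis plan, which is not at hand. All of this stands. A reader might infer that the rule makes the primary estimate invalid, and the article does not support that. What remains is that the article states the rule itself, so an analysis plan that follows it inherits a model settled by chance, however complete its variable list.

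**On baseline.** A reader might infer that the plan certainly loses precision. It may not: if considering baseline means adjusting the month-6 value for it, the model already is an ANCOVA. The loss is conditional on the other reading and shrinks as rho rises. At rho 0.7 and above the change-score test itself exceeds 80% power under the article's SD and difference, so the figures at 0.5 or 0.6 alone would overstate the matter. The objection leaves the ambiguity standing.

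**On the named covariates.** It is not certain that sex, age and education level are confined to ordinal outcomes. The next sentence of the article gives that model an identity link and a normal outcome, which suits continuous data. Nothing in the article shows how strongly these variables predict HbA1c here.

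**Conclusion.** The point holds in two parts of different strength.

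First, and firmly: the article selects covariates by a threshold smaller than one standard error. About 46% of variables at 111 per arm, and about 50% at 89, pass it by chance. This needs only the arm sizes and sound randomisation. The consequence is an adjustment set that depends on chance and may omit prognostic covariates.

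Second, and conditionally: the role of baseline is ambiguous. If it is a repeated measure, the analysis has 2/(1 + rho) times the variance of ANCOVA. For an assumed rho of 0.4 to 0.8, ANCOVA variance is 30% to 10% lower, and the power difference runs from 15 points down to 2. If baseline is a covariate, there is no loss.

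A reader might also infer that the point weighs more because the trial falls short of its stated power. Whether 222 participants deliver that power is a separate question about the sample size calculation and adds nothing here. The change is worth making because it replaces a poor stated rule at almost no cost.

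**What to change.** In the Data analysis section, state the primary analysis as an ANCOVA of month-6 HbA1c on arm, or an equivalent mixed model with baseline means constrained to be equal. Adjust for baseline HbA1c and a fixed covariate set, whatever imbalance is observed. Sex, age and education level, which the article already names for the GEE, are a natural choice; any other set would serve if it is fixed before the data are seen. Report the adjusted mean difference in HbA1c with its 95% CI; Cohen's d can supplement it. Keep standardised mean differences as a description of the arms and delete the 0.1 trigger, both for the ANOVA ("covariates that are imbalanced in control and intervention groups when conducting ANOVA") and for the GEE.

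The cost is wording only. HbA1c is already taken at entry, and the three covariates are already planned for analysis.
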